## Abstract

**Background:**

Kaposi sarcoma (KS) is a mesenchymal malignancy induced by human herpes virus-8 (HHV-8). Whilst combined anti-retroviral therapy (cART) has substantially reduced the incidence of KS in people living with HIV (PLWH), KS remains the commonest neoplasia in this population. In up to 15–20% of cases, KS fails to respond to cART. T-cells immune exhaustion is thought to play a central role in mediating KS development and progression in PLWH receiving cART. The high reliance of PD-1 in shaping the cART-refractory phenotype poses a strong rationale for the use of PD-1 blocking antibodies against KS.

**Aims:**

StarKap is a phase Ib, open label, single arm study aiming at evaluating the safety, tolerability of dostarlimab- an anti PD-1 antibody- in cART-refractory KS. Secondary endpoint is the evaluation of overall response rates by AIDS Clinical Trial Group (ACTG) criteria complemented by RECIST v1.1 in patients with visceral disease.

**Methods:**

The trial will enrol 20 patients in total. After completion of the screening procedures, participants will receive the first dose of dostarlimab within 28 days. Dostarlimab will be administered at the dose of 500 mg evry 3 weeks for the first 5 cycles, and at 1000 mg every 6 weeks thereafter. Treatment will continue until disease progression, unacceptable toxicity, or completion of 1 year of treatment. The first 6 patients will be enrolled in a safety-lead-in phase, if no dose-limiting toxicities (DLTs) will occur within the 21 days in the first 6 participants, trial will continue. Patients will be monitored for the emergence of adverse events until 90 days after the last dose of treatment. Tumour response will be assessed as objective response rate (ORR) at cycle 4, cycle 8 and end of treatment. Tissue, bloods, and stool samples will be collected at baseline, on treatment and at end of treatment to satisfy the related translation plan.

## Background and rationale

### Background

HIV associated Kaposi’s sarcoma (KS) is a mesenchymal malignancy associated with Human-Herpesvirus 8 (HHV-8) infection, occurring in people living with HIV (PLWH) [1]. The grade of immunosuppression and the CD4 count represent the main risk factor for developing KS in PLWH. Therefore, the incidence of KS has drastically dropped since the widespread availability of combined anti-retroviral therapy (cART). However, PLWH remain a higher risk of KS compared to the general population even in the case of well-controlled viremia, and about 15% of HIV associated KS develop or progress despite HIV control maintained for at least 3 months, and preserved CD4 count (> 100 cells/µL) [1]. These cases are defined as cART-refractory KS, and palliative cytotoxic chemotherapy (e.g., liposomal doxorubicin, paclitaxel, bleomycin) remains the only avaiable therapeutic option. Despite initial response occurring in up to 60% of patients, most of the cases recur with consequent long-term need for chemotherapy leading to cumulative toxicities and impaired quality of life [2]. Immuno-modulatory agents like lenalidomide and pomalidomide are emerging as promising therapy for KS [3], however their use is not currently licensed in all countries and toxicity of these therapies is significant. We have therefore designed a phase Ib trial testing dostarlimab (anti-PD1) in patients affected by cART-refractory KS.

### Rationale

Immune exhaustion is emerging as a leading mechanism responsible for the development and progression of cART-refractory KS. Studies specifically conducted in patients affected by cART-refractory KS have reported higher grade of CD8 + T cells mitochondrial dysfunction [4] and features of immune senescence in PLWH and KS compared to PLWH without KS [5]. HHV-8 infection is thought to be pivotal in leading to immune dysfunction: in fact, both pre-clinical and clinical studies have reported HHV-8 to directly induce immune exhaustion by leading to PD-1/PD-L1 pathway overactivation in both tumour [6] and immune cells [7]. Furthermore, translational experiments from our group have demonstrated the presence of immune infiltrate to be prominent in KS lesions, and to be associated with PD-L1 over-expression in cART- refractory KS tumour samples [8]. These results suggest the PD-1/PD-L1 pathway to be exploited by KS tumour cells to evade CD8 + T cells attack within the tumour micro-environment. Reverting this mechanism by direct PD-1 inhibition might be able to restore adequate CD8 + T cells function against both HHV-8 and KS.

Immune-checkpoint inhibitors (ICIs) have been tested both as monotherapy (pembrolizumab) [9] and in combination (ipilimumab plus nivolumab) [10] in KS occurring in people without HIV, with promising results. Pembrolizumab has been recently tested in a single arm phase II study, with an objective response rate (ORR) of about 70% according to the AIDS clinical trial group (ACTG) criteria [9]. Among the 17 patients treated with pembrolizumab, 6 had not received any prior chemotherapy. Similarly, a phase 2 study testing the combination of the anti CTLA-4 antibody ipilimumab plus the anti PD-1 nivolumab has been tested in KS patients without HIV, after progression on at least 1 line of prior systemic therapy, showing an ORR of 87% according to RECIST without new safety concerns [10]. In both trials, responses were independent from the type and the number of previous treatment lines.

So far, ICIs in HIV-associated KS have been tested in only one dedicated prospective trial. This is a phase Ib trial conducted in the US, which recently reported on the safety and efficacy of pembrolizumab (anti-PD1) in HIV-associated KS. The trial included patients with undetectable viral load and a CD4 count of at least 50 cells/µL. Among the 32 patients enrolled, 31% ad at least one immune-related AE (irAE) with 25% required systemic steroids. The ORR according to the ACTG criteria was 62.1%. The safety and the efficacy profiles did not differ according to the CD4 count [11]. Furthermore, no HIV-related complications, nor CD4 count alterations were reported during the study. This has been also confirmed in the other available studies testing ICI in PLWH for different oncological indications [12–14]. A cohort (N = 15) of patients affected by KS was also included in the AIDS Malignancy Consortium 095 Study, a multicentre phase I study, which tested nivolumab (anti-PD1) at 3 mg/kg every 2 weeks in PLWH with undetectable HIV-RNA and CD4 count of at least 100 cells/µL affected by solid tumours or KS. The incidence of adverse events of any causes in the whole cohort was 80%, and 25% of the participants experienced grade 3 or higher adverse events. Fatigue, nausea, diarrhea, rash, and lymphopenia were the most common AEs at least possibly related to nivolumab occurring in more than 10% of the subjects. All of which of grade 1 or 2. No significant changes in the HIV-RNA or CD4 count occurred in the study. The ORR per ACTG criteria in the KS subgroup was 40% [12].

No safety nor efficacy data are currently available for dostarlimab in PLWH. According to the latest product’s brochure, with a data cut-off in April 2024, overall, 2087 participants without HIV have been treated in clinical trials with dostarlimab either alone or in combination therapy. The safety profile of the monotherapy from the GARNET [15] phase III trial, enrolling 494 patients affected by advanced endometrial cancer progressing to platinum-based chemotherapy, reported an incidence of all causes adverse events in any patients, with nausea (53.9%), alopecia (53%) and fatigue (51.9%) being the most common. The incidence of grade 3 or higher adverse events was 70.5% in the dostarlimab arm. The most common immune-related (AE) were hypothyroidism (11.2%), skin rash (6.6%), arthralgia (5.8%), and alanine aminotransferase increase (5.8%) [15].

These results, along with the emerging data supporting the safety of immune checkpoint inhibitors in PLWH, prompt the specific investigation of this approach in cART-refractory KS.

We have therefore designed an investigator lead study to assess the safety and activity of dostarlimab- an anti PD1 antibody- in a cohort of 20 patients affected by cART- refractory KS.

## Clinical trial registration

NCT05646082 (ClinicalTrials.gov). Registration date: 02–12–2022. Star date: 26–05–2023.

## Methods

### Trial design

The StarKap study is a single centre open label phase Ib trial assessing the safety, tolerability and preliminary efficacy of dostarlimab in patients affected by cART-refractory KS. The trial is sponsored by Imperial College London and is currently open to recruitment at Chelsea & Westminster Hospital, in London, UK.

A phase Ib, single-arm, open label study describing safety and tolerability of dostarlimab is necessary to answer the question of feasibility of anti-PD-1 immunotherapy in PLWH and KS. No dose-escalation was deemed necessary in this population due to the non-linear relationship between exposure and immune-mediated toxicity and the lack for dose-limiting toxicities observed in dose escalation studies of dostarlimab [15, 16].

The study will enrol 20 adult patients aged (aged ≥ 16 years) affected by HIV-related KS, fulfilling the criteria of cART-refractory KS. To this end, patients will be required to have KS that progressed or remained stable after at least 3 continous months of cART, with HIV-RNA < 200 copies/ml and CD4 count of at least 100 cell/µL at screening. Upon completion of screening procedures and confirmation of eligibility, patients will start treatment with dostarlimab within 28 days from screening. Dostarlimab will be administered intra-venously according to summary of product characteristics, at the dose of 500 mg every 3 weeks for the first 4 cycles and at 1000 mg every 6 weeks for the following cycles. Dostarlimab will be continued until completion of 1 year, loss of clinical benefit, inacceptable toxicities or withdrawal of consent, whichever comes first.

A safety lead-in phase will initially require a total of 6 patients, who will be observed for the emergence of dose-limiting-toxicities (DLTs) over a 21-days window from dosing. Following discussion within the trial steering committee it was opted to maintain a standard 21-days safety window for the first 6 subjects with a particular focus on the assessment of events of immune-reconstitution as well as qualitative and quantitative changes in parameters reflective of HIV control. The decision to enrol 6 subjects for the initial safety lead-in phase is in line with standard clinical trial design practice for early-phase trials. This number is generally considered sufficient to detect any early DLTs [17].

Once all the 6 patients have completed the 21-day safety window observation, trial steering committee (TSC) will review the AE profile and, in the absence of DLTs advise on continuation of recruitment to the subsequent expansion phase leading to enrolment of 20 patients in total. If ≥ 1 DLTs will occur within the first 21 days in the patients enrolled in the safety-lead-in phase, the trial will be prematurely interrupted. During the TSC review, the enrolment of new patients will be paused. In the absence of AEs preventing to do so, the treatment of the first 6 patients will continue as planned, without waiting for the TSC review. The definition of DLTs is reported in Table 1. No dose-reductions are allowed. In general, dostarlimab must be withheld for drug-related toxicities of grade 3, but may be resumed upon recovery to Grade ≤ 1; dostarlimab will be permanently discontinued for any drug-related AE of grade 4. Treatment delays for up to 21 days are permitted in the case of AEs. Any AEs requiring a treatment interruption > 21 days will prompt treatment interruption.

**Table 1 Tab1:** Definition of dose limiting toxicities according to CTCAE v.5

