
### Statistical analysis

With safety being elected as primary clinical endpoint for the study, no power calculation for hypothesis testing was required to formally power the study. Justification for a sample size of 20 subject was based on previous experience in the use of pembrolizumab in HIV-associated cancers [9, 22].

An interim analysis on adverse events will be conducted after the 6 th subject clears the 21-days safety window. Pending review of safety data by the trial steering committee in the first 6 subjects, in the absence of significant toxicity, the study will continue to the recruitment of the remaining 14 subjects without pause.

The final efficacy analysis on the whole will be conducted at the end of the study after the last patient has completed the treatment.

The safety population will include all subjects receiving at least one dose of dostarlimab. All participants who receive at least one dose of dostarlimab and undergo efficacy evaluation will be included in the efficacy population. No patients will be replaced as this would introduce bias; drop-out is likely to be informative in this population.

The primary outcome will be presented using descriptive measures of safety such as frequencies and percentages of adverse events grouped as categorical variables and means and standard deviations for normally distributed continuous variables.

Efficacy endpoints will be estimated descriptively by documenting ORR and progression free survival rates (PFSR) at 12-weekly timepoints. Progression free survival will be estimated using the Kaplan–Meier method from screening to progression or death. The PFSR estimates the proportion of participants who do not progress and are alive at 12 weeks timepoint.

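### The lead-in's stated property is too strong: six patients reliably reveal only common DLTs, not any early DLT

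*Protocol article*

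**What the plan says.** In Trial design the article sets the lead-in size and window: "A safety lead-in phase will initially require a total of 6 patients", observed for DLTs "over a 21-days window from dosing". It gives two reasons for the number six: conformity with usual early-phase practice, and the property "This number is generally considered sufficient to detect any early DLTs". A reference is cited. No DLT rate, probability or confidence level accompanies the statement.

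The same section gives the rule. If one or more "DLTs will occur within the first 21 days in the patients enrolled in the safety-lead-in phase, the trial will be prematurely interrupted". Otherwise the trial steering committee reviews the adverse event profile and will "in the absence of DLTs advise on continuation of recruitment to the subsequent expansion phase leading to enrolment of 20 patients in total". DLTs are defined in Table 1.

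Statistical analysis adds that "no power calculation for hypothesis testing was required to formally power the study". It also makes continuation to the remaining 14 patients depend on the committee's review and the absence of significant toxicity. Safety observation does not end with the lead-in. The abstract states: "Patients will be monitored for the emergence of adverse events until 90 days after the last dose of treatment".

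**The concern.** Whether six patients can detect a toxicity depends on how common that toxicity is. Saying that six suffice for any early DLT sets no lower limit on the rate, and no small sample can have that property. A toxicity affecting one patient in ten or one in twenty can easily be absent from six patients.

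This matters because safety is the primary objective and the Rationale section states that there are no dostarlimab safety data in people living with HIV. The article describes a DLT assessment only for the first six patients, and a clean result there opens the expansion to 20. The committee and later readers should know what 0/6 does and does not show, and the sentence as written tells them something the design cannot deliver.

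**Working it through.** **Inputs.** Lead-in size n = 6, a 21-day window, and a trigger of at least one DLT (all from Trial design). Total enrolment is 20. The true DLT rate p is an assumption, because the article gives no target, tolerable or expected rate. The nearest figure in the Rationale section is 25% with grade 3 or higher adverse events in the nivolumab study, which is not a 21-day DLT rate. I therefore show a range.

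**The plan's own figure.** There is none to reproduce: the property is stated in words only.

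**Step 1: chance of seeing at least one DLT.** With independent patients and a common rate p, P(at least 1 in 6) = 1 − (1 − p)^6.

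| True rate p | P(0 in 6) = (1 − p)^6 | P(at least 1 in 6) |
|---|---|---|
| 5% | 0.95^6 = 73.5% | 26.5% |
| 10% | 0.90^6 = 53.1% | 46.9% |
| 15% | 0.85^6 = 37.7% | 62.3% |
| 20% | 0.80^6 = 26.2% | 73.8% |
| 25% | 0.75^6 = 17.8% | 82.2% |

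The right-hand column is also the chance that the one-DLT rule is triggered at that rate.

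**Step 2: rates that six patients detect with a given probability.** Solving for p at detection probability t gives p = 1 − (1 − t)^(1/6).

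- t = 50%: 1 − 0.50^(1/6) = 10.9%
- t = 80%: 1 − 0.20^(1/6) = 23.5%
- t = 90%: 1 − 0.10^(1/6) = 31.9%
- t = 95%: 1 − 0.05^(1/6) = 39.3%

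A rate below 10.9% is more likely to be missed than seen. Detection that most would call reliable needs a rate of about a quarter to two-fifths.

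**Step 3: what a clean lead-in excludes.** After 0/6, the one-sided 95% upper limit is 1 − 0.05^(1/6) = 39.3%. The two-sided 95% Clopper-Pearson upper limit is 1 − 0.025^(1/6) = 45.9%.

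**Step 4: what all 20 patients could add.** After 0/20, the one-sided 95% upper limit is 1 − 0.05^(1/20) = 13.9%. The clean-lead-in requirement does not disturb this limit, because (1 − p)^6 × (1 − p)^14 = (1 − p)^20. With a non-zero total it does matter: expansion happens only after 0/6, so every event must come from the later 14 patients and the proportion out of 20 is biased low.

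**The case against.** The sentence is hedged, appeals to convention and cites a source that is not at hand. It states no number, so no number is contradicted, and calling it an arithmetic error would be wrong. That stands. But the hedge only says who holds the view; the view is still offered as a reason for choosing six, and no citation alters the binomial result.

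Six patients with a stop at the first DLT is the strictest threshold possible for that size. Nothing here shows the design to be invalid, and no larger lead-in is called for. The article also draws on more than six patients: it cites 2087 people without HIV treated with dostarlimab, anti-PD-1 studies in people with HIV, and an absence of DLTs in dostarlimab dose escalation. All of this limits the consequence; none of it makes the sentence true.

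Three stronger readings are tempting, and the article does not support them:

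- A reader might infer that the whole decision to continue or stop rests on this sentence. It does not: the rule operates whatever detection probability is claimed, and the committee also reviews the adverse event profile.
- A reader might infer that detection is poor at every rate below about 20%. It is 62.3% at 15%. The result at 10% is also a narrow split, 53.1% missed against 46.9% seen, at an assumed rate just under the 10.9% break-even.
- A reader might infer that 0/6 will be reported as having excluded DLTs. Nothing in the text says so. A clean lead-in permits further recruitment, and the primary endpoint counts adverse events up to 90 days after treatment ends.

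Finally, the 20-patient tabulation adds an analysis and does not correct the sentence. That is fair, and it is offered below on those terms.

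**Conclusion.** The point holds as a misstated design property. Six patients do not suffice to detect any early DLT. Over assumed true rates of 5% to 25%, the chance of seeing at least one runs from 26.5% to 82.2%, and 0/6 leaves rates up to 39.3% compatible with the data (one-sided 95%). These figures assume independent patients with a common rate, all six assessable over the 21 days. The rates themselves are illustrative, but the conclusion does not hang on any one of them, because an unqualified claim about any DLT has no lower bound. The correction changes what a clean lead-in can be said to show; it leaves the conduct of the trial as it is.

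**What to change.** Replace the sentence in Trial design with the actual property, for example: *Six patients give a 26.5%, 46.9%, 62.3%, 73.8% and 82.2% chance of observing at least one DLT if the true 21-day rate is 5%, 10%, 15%, 20% and 25%; observing none excludes only rates above 39.3% (one-sided 95% limit).* Keep the lead-in size and the stopping rule unchanged.

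As a descriptive addition, apply the Table 1 definitions to the first 21 days of all 20 treated patients and report the count with an exact interval, attaching no new stopping rule. Show the first 6 and the later 14 separately beside the total, for the reason given in Step 4.

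The cost is a less favourable stated property and one further table. The table should need no new data collection, since adverse events are already graded by CTCAE v5.0 and followed in all treated patients.

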**Dose limiting toxicities**	
Any treatment-related Grade ≥3 nonhematologic clinical toxicity excluding: − Nausea and vomiting resolving to ≤ grade 1 within 48 hours − Grade 3 diarrhea with duration < 48 hours − Grade 3 fatigue with duration < 7 days − Infusion related reaction − Any treatment-related non hematology toxicity specifically defined as: − ≥Grade 2 uveitis, eye pain, or blurred vision that does not resolve with topical therapy within 2 weeks − ≥Grade 2 immune related endocrine toxicity that requires hormone replacement (except Grade 2 thyroiditis or thyroid dysfunction) − ≥Grade 2 colitis or diarrhea that persists for ≥ 7 days despite adequate steroid therapy − Any toxicity that results in a treatment delay of ≥7 days − Any treatment-related Grade ≥3 non-hematologic laboratory abnormality if: − Medical intervention is required to treat the patient, or − The abnormality leads to hospitalization, or − The abnormality persists for ≥7 days − Any treatment-related hematologic toxicity specifically defined as: − Grade 4 thrombocytopenia for ≥7 days, or grade 3 or 4 associated with bleeding or requiring platelet transfusion − Grade 4 neutropenia for ≥7 days, or grade 3 or 4 associated with infection or febrile neutropenia − Grade 4 anaemia, or grade 3 anaemia requiring blood transfusion	

Tumoral skin biopsies will be collected at baseline, during treatment (cycle 4), and at the end of treatment to complete the associated translational plan. Stools, bloods and urine samples will be collected at baseline, at cycle 4, at cycle 8 and end of treatment.

Participants will be followed at 30 and 90 days after removal from protocol therapy or until death, whichever occurs first. Overall survival will be followed for 2 years following the last dose of protocol therapy.

The trial scheme is summarised in Fig. 1.

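### Table 1 exempts infusion reactions from the DLT definition with no grade limit, so a fatal reaction meets no DLT item and a grade 4 reaction meets one only on a favourable reading

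*Protocol article*

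**What the plan says.** All references are to the protocol article.

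- **Table 1** makes a treatment-related non-haematological clinical toxicity of grade 3 or worse a DLT, subject to four exclusions: nausea and vomiting that settle within 48 hours, grade 3 diarrhoea shorter than 48 hours, "Grade 3 fatigue with duration < 7 days", and "Infusion related reaction". Further specific DLT criteria follow, among them "Any toxicity that results in a treatment delay of ≥7 days".
- **Trial design** sets the stop: "If ≥ 1 DLTs will occur within the first 21 days" in the lead-in, the trial is interrupted. The steering committee "will review the AE profile and, in the absence of DLTs advise on continuation of recruitment". The **Abstract** puts it more simply: "if no dose-limiting toxicities (DLTs) will occur within the 21 days in the first 6 participants, trial will continue".
- **Trial design** observes DLTs "over a 21-days window from dosing", so the first infusion falls inside the window. On individual treatment it says "dostarlimab will be permanently discontinued for any drug-related AE of grade 4".
- **Statistical analysis** makes recruitment of the other 14 patients conditional on the committee's safety review finding no significant toxicity, a term the article does not define.

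**The concern.** The stop is binary and depends entirely on what Table 1 calls a DLT. An exclusion without a grade limit removes the whole range from grade 3 to grade 5 from the general criterion. That inverts the ordering of severity. Treatment-related grade 3 fatigue that lasts 7 days ends the trial by rule, but a fatal infusion reaction ends it only if the committee so decides.

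Safety is the primary objective, and the Rationale states that there are no dostarlimab safety data in people living with HIV. A mandatory stop should not leave its most serious events to interpretation.

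**Working it through.** **1. The four exclusions side by side.** The table's indentation is lost in the text at hand. Taking the first four items as exclusions and the rest as separate DLT criteria is an inference. It is the only reading under which the eye, endocrine and haematological items make sense.

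| Exclusion | Grade limit | Time or resolution limit | Can a fatal event be excluded? |
|---|---|---|---|
| Nausea, vomiting | none | to grade 1 or lower within 48 hours | no, it cannot resolve |
| Diarrhoea | grade 3 | under 48 hours | no |
| Fatigue | grade 3 | under 7 days | no |
| Infusion reaction | none | none | yes |

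Only the last row lets a fatal event leave the general criterion.

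**2. Does another Table 1 item catch it?** The eye, endocrine, colitis and haematological items concern other toxicities. The intervention and hospitalisation conditions apply only to laboratory abnormalities. That leaves the delay item.

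- *Grade 5.* A death is not a treatment delay. No item applies on its plain wording.
- *Grade 4, non-fatal.* The patient stops dostarlimab permanently. The delay item applies if (a) a permanent stop counts as a delay of at least 7 days and (b) the DLT is dated by the onset of the toxicity.

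**3. Why dating matters.** Dose 1 is on day 1 and dosing is every 3 weeks, so dose 2 is due on day 1 + 21 = 22. A 7-day delay is complete on day 22 + 7 = 29, after the 21-day window. Dated by completion, the item could never fire for dose 2; dated by onset, it can. The article states neither (a) nor (b).

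**4. Size.** The documents give no rate of grade 4 or 5 infusion reactions and no operating characteristics for the lead-in, so there is no stated figure to reproduce. Let u be an assumed per-patient rate of grade 4 or 5 infusion reactions and p an assumed rate of all other DLTs.

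Chance of at least one grade 4 or 5 reaction in 6 patients = 1 − (1 − u)^6. For example, at u = 1%, 1 − 0.99^6 = 5.9%.

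Chance of no DLT in 6 patients: (1 − p)^6 if such reactions never count, and [(1 − p)(1 − u)]^6 if they always count and are independent of other DLTs.

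| | not counted | u = 0.1% | u = 0.5% | u = 1% | u = 2% |
|---|---|---|---|---|---|
| At least one reaction in 6 | – | 0.6% | 3.0% | 5.9% | 11.4% |
| No DLT, p = 5% | 73.5% | 73.1% | 71.3% | 69.2% | 65.1% |
| No DLT, p = 10% | 53.1% | 52.8% | 51.6% | 50.0% | 47.1% |
| No DLT, p = 20% | 26.2% | 26.1% | 25.4% | 24.7% | 23.2% |

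If reactions and other DLTs never fall in the same patient, (1 − p − u)^6 at p = 10% gives 52.8%, 51.4%, 49.7% and 46.4%. All these differences are upper limits on what the present wording could miss, because the delay item may already catch the non-fatal reactions.

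**The case against.** The strongest reply is that little is left uncovered.

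- The delay item refers to any toxicity, so the exclusion from the general criterion does not reach it. Onset dating is the only reading that gives the item any content for dose 2. Treating a 7-day postponement as a DLT but a permanent stop for the same toxicity as none is strained. **This largely stands:** grade 4 is plausibly covered, though the text does not say so.
- Enrolment is paused while the committee reviews the whole adverse event profile, and Statistical analysis requires that there be no significant toxicity. **This stands as a backstop.** A reader might infer that the trial would carry on after a fatal infusion reaction. The documents do not support that, since a treatment-related death could hardly pass such a review. What is lost is the automatic stop.
- Exempting infusion reactions is a coherent choice when one DLT in 6 ends the trial, and Trial design says that the lead-in focuses on immune reconstitution and HIV control. Nothing in the article suggests that HIV alters the risk of infusion reactions, and it reports 2087 participants without HIV already treated. **This stands for grade 3.** A reader might infer that slow-resolving grade 3 reactions should count as well. That is a clinical trade-off, and the documents do not settle it. The argument is weak for grades 4 and 5, and the article gives no reason for exempting those.
- A grade qualifier might sit in the full protocol. This is possible but not shown; Trial design presents Table 1 as the DLT definition.

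**Conclusion.** The point holds in a narrow form and is minor. On the wording of Table 1, a fatal infusion reaction in a lead-in patient is not a DLT. A grade 4 reaction is one only if permanent discontinuation counts as a delay and the DLT is dated by onset. For these events the mandatory stop gives way to committee judgement.

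The conclusion rests on the missing grade limit and on the reading of the table's layout given above. It does not rest on the assumed rates, which only show that the effect on the lead-in is small if such reactions are rare.

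The point bears on the stop only if the lead-in is still running, and the article does not say whether it is. It gives a start date of 26 May 2023, cites product data to April 2024 (311 to 340 days later), and describes the trial as open to recruitment.

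**What to change.** In Table 1, put the words Grade 3 in front of the infusion reaction exclusion, to match the diarrhoea and fatigue items. Any treatment-related grade 4 or 5 infusion reaction within the 21-day window is then a DLT, however the delay item is read. Do not add a time limit for grade 3 reactions: under a one-in-six stop this would create further trial-ending events, and that choice belongs to the sponsor's clinicians.

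The cost is a one-line amendment, with no added visits or data. The downside is a slightly higher chance that the lead-in stops the trial. The documents cannot give its size; under the assumed rates it is at most the differences tabulated above, and less if grade 4 reactions already count through the delay item. If the lead-in is complete, the change has no effect on the stop.

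### The DLT definitions, the 21-day window and the timing of the steering committee's go decision do not fit together: one criterion cannot be established by day 21, and others only for early-onset events

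*Protocol article*

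**What the plan says.** The Trial design section takes six lead-in patients, "who will be observed for the emergence of dose-limiting-toxicities (DLTs) over a 21-days window from dosing". Dostarlimab is given at "500 mg every 3 weeks for the first 4 cycles". The Abstract gives a different number of 3-weekly cycles, but the interval from dose 1 to dose 2 is 3 weeks in both places.

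The committee reviews the adverse events "Once all the 6 patients have completed the 21-day safety window observation" and, if there are no DLTs, advises on going on to the expansion phase. One or more DLTs in the first 21 days interrupts the trial. The Statistical analysis section repeats the trigger: the interim look comes after the sixth subject clears the window, and 14 more subjects follow.

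Table 1 defines the DLTs. One entry is "Any toxicity that results in a treatment delay of ≥7 days", with no grade attached. Others need persistence:

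- colitis or diarrhoea lasting 7 days despite steroids;
- a laboratory abnormality lasting 7 days;
- grade 4 thrombocytopenia or neutropenia lasting 7 days;
- grade 3 fatigue, which is exempt while shorter than 7 days;
- eye events that do not settle with topical treatment within 2 weeks.

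The article does not say whether a DLT is dated by onset or by the day its criterion is met. Nor does it say what happens to events still open at day 21.

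**The concern.** The lead-in is the only trial-level stopping rule described, and a single DLT decides it. The article states that there are no dostarlimab safety data in people living with HIV, so this decision carries weight for the 14 patients who follow.

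A rule that turns on the absence of DLTs works only if every listed DLT can be recognised by the time the rule is applied. Here one listed event cannot be, and several others can be only if they start early. Followed literally, the rule can return no DLT while a qualifying event is still running its course.

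**Working it through.** The plan states no DLT rate, power or operating characteristic for the lead-in, so there is no figure of its own to reproduce. The counts agree: 6 + 14 = 20.

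**Step 1. Calendar check.** Days are counted from dose 1. Inputs are the 21-day window and 3-week interval (Trial design) and the durations in Table 1. Latest onset that can be established by day 21 = 21 − required duration. Earliest day a delay can be established = day dose 2 is due + 7.

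| Table 1 criterion | Calculation | Result |
|---|---|---|
| Dosing delay of a week or more | 21 + 7 | day 28 at the earliest, 7 days after the window closes |
| 7-day criteria | 21 − 7 | onset by about day 14 |
| 2-week eye criterion | 21 − 14 | onset by about day 7 |

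For colitis or diarrhoea the limit is earlier still if the 7 days run from the start of steroids.

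**Step 2. Two ways of dating a DLT.**

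- *By the day the criterion is met.* The delay criterion falls outside the window in every patient and can never count. Late-onset 7-day and 2-week events do not count either.
- *By onset.* Every criterion can count in principle. But an event starting on day 21 needs follow-up to about day 28 (7-day criteria) or day 35 (eye criterion). A delay of dose 2 also needs follow-up to day 28. The review is triggered at the sixth patient's day 21, so such events in the latest patients are still unclassified.

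**Step 3. Size.** Assumptions, none from the documents: a true DLT rate p of 5, 10 or 20%, and onset uniform over 21 days. The share of 7-day events that can be established by day 21 is then 14/21 = 67%, so one third is missed. For the eye criterion the share is 7/21 = 33%.

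- Full ascertainment: 1 − (1 − p)^6
- One third missed in the sixth patient only: 1 − (1 − p)^5 × (1 − 2p/3)
- One third missed in all six: 1 − (1 − 2p/3)^6

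| P(at least one DLT seen in six) | p = 5% | p = 10% | p = 20% |
|---|---|---|---|
| Full ascertainment | 26% | 47% | 74% |
| One third missed, sixth patient only | 25% | 45% | 72% |
| One third missed, all six | 18% | 34% | 58% |

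For example, at p = 20% the second row is 1 − 0.8^5 × (1 − 0.133) = 1 − 0.328 × 0.867 = 0.716.

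The last row treats every DLT as a 7-day type and cuts all six patients at exactly day 21. DLTs that qualify only through a dosing delay would be missed entirely if dated by the day the criterion is met.

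**The case against.** The best defence is that the window concerns the emergence of toxicity. On that reading the toxicity must start within 21 days and the delay or persistence only qualifies it, so nothing in Table 1 is excluded. A day-18 event confirmed on day 28 would still stop the trial, because the stopping sentence is not tied to the meeting. The committee sees the whole adverse event profile, and enrolment is paused during its review. Patients enrolled earlier will often be past day 28 or day 35 by then.

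Much of this stands, and it limits the size of the problem. It does not remove it: the article does not adopt onset dating, and nothing makes the committee wait for open events.

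A reader might infer more than the documents support:

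- *That several criteria are impossible to meet.* Only the delay criterion is; the rest are restricted to early onset.
- *That a third of all DLTs is lost.* Most grade 3 or higher non-haematologic clinical toxicities count at once. So do endocrine events needing hormone replacement, laboratory abnormalities needing intervention or hospitalisation, and complicated cytopenias.
- *That one early drop-out blocks the review, given "No patients will be replaced as this would introduce bias".* That sentence follows the analysis populations and does not mention the lead-in. Stopping treatment does not end follow-up, no early loss rate is given, and a definition of evaluable patients may sit in the full protocol.
- *That six is too few.* "This number is generally considered sufficient to detect any early DLTs" is a general statement resting on a cited source. The full-ascertainment figures apply to any six-patient lead-in with this rule and show no error in this one.

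**Conclusion.** The inconsistency is real and follows from the article's own calendar, without any assumed rate. The delay criterion cannot be established before day 28, the go decision is triggered at day 21 of the sixth patient, and neither way of dating a DLT closes the gap.

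Its size is uncertain. It depends on the unknown share of DLTs defined by duration or delay, and on how closely together the six are enrolled. At the assumed rates of 5/10/20%, the loss of detection is about 1 to 2 percentage points if one third is missed in the sixth patient only, and about 8 to 16 points if one third is missed in all six. These figures rest on uniform onset and on 7-day criteria. The documents do not show that a wrong go decision would happen, only that the rule as written permits one.

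**What to change.** Reconcile the Trial design text, Table 1 and the Statistical analysis section on two points:

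1. State whether a DLT is dated by its onset or by the day its criterion is met.
2. Make the go decision account for events still open at the sixth patient's day 21, so that it is not final until they can be classified against Table 1.

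This does not require choosing any DLT criterion, dose or window length. If the lead-in review has already taken place (the article gives a start date in May 2023), the sponsor should record how events open at day 21 were handled.

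The cost is wording, plus a delay to the review of about 1 to 2 weeks (day 28 or day 35 instead of day 21), and only when an event is open. No extra patients are needed.
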